### Health outcome assessment with a sanitation calendar

We distributed a sanitation calendar to all registered households beginning in December 2015 and asked mothers or caregivers to mark “O” or “X” depending on the presence of diarrheal disease of her youngest child every day over the 12-month period of longitudinal observation from December 2015 to November 2016. WaSH promoters have been monitoring the recording status of the sanitation calendar on a weekly basis and continue to educate and encourage mothers or caregivers to continue recording appropriately.

We devised an incentive mechanism to encourage the mothers or caregivers to record diarrheal episodes on the sanitation calendar properly by establishing a system where a well-maintained calendar can be used as a voucher. A well-recorded calendar, regardless of whether it contains Os or Xs will be exchanged with a gift-in-kind, probably sanitation-related materials such as soaps, nail clippers, toothpastes, or the like. WaSH promoters will take a photo of the sanitation calendar using a mobile phone and submit to a supervisor and the team leader. For the study, diarrhea is defined as three or more watery stools in 24 hours according to the WHO definition.

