### Study design

The study was approved by the National Research Ethics Review Committee under the Ministry of Science and Technology, Federal Democratic Republic of Ethiopia (NRERC 3.10/032/2015; July 29, 2015) and was registered as an ISRCT on March 13, 2015 (ISRCTN82492848).

In the study, a *gott*, the Amharic word for village, was taken as the randomization unit because we expected that improved latrines could impact diarrheal transmission across households within a *gott*, where people interact with one another most closely. All the interventions related to latrine improvement will be performed at each *gott* level.

A phase-in and factorial design will be used for the study. The intervention for improving latrines will be implemented in the intervention arm during the first phase, and the comparable intervention will be performed in the control arm during the second phase. During the second phase, a water pipe will be connected to the *gotts* in the intervention arm. After the second phase is completed, the control group will receive the intervention of a water pipe connection. With the design, we will investigate not only the effect of improved sanitation but also the combined effects of improved water and sanitation interventions.

A preliminary survey was carried out to develop this water, sanitation, and hygiene (WaSH) project intervention design in March to May 2013. Water pipes will be connected to 212 *gotts*, of which, 48 *gotts* were selected as the study area of the trial. In the intervention *gotts*, the procedures of the Community-Led Total Sanitation including pre-triggering, triggering, and follow-up will be carried out for latrine improvement beginning in November 2015 and will continue to October 2016.

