### Primary endpoint

The primary endpoint of the study is diarrheal prevalence in children under 5 years of age. We will use 7-day prevalence of reported diarrhea in the household, which will be based on parental reports. The survey will be conducted five times at the household level: the first four rounds will be carried out in the first phase to explore the effect of improved latrines, and the last one, in the second phase to assess the combined effects of improved water and sanitation.

In addition to diarrheal prevalence, we will measure diarrheal incidence and diarrheal duration. For documentation of diarrheal incidence and duration, we will have the mother or caregiver record the diarrheal episodes of her youngest child on a “Sanitation Calendar” (Amharic language: *Yenezehenna Gize Saleda*) on a daily basis (Fig. 2).

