### Household sampling methods

A list of households with children under 5 years of age was established by four supervisors in each *gott* before the baseline survey. Supervisors required 8 days to produce a complete household list for all 48 *gotts*. Using SPSS 21 Statistics software, the survey team leader randomly sampled 25 households from each *gott*. Enumerators will recruit the youngest child under five from each household, from the fifth week of October through the second week of November 2015. If the mother or a household caregiver is absent at the time of the recruitment visit, the enumerator will revisit the same household two more times. If the mother or caregiver refused to be registered, a neighboring household with a child under 5 was visited to replace the household (Fig. 3).

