### Intermediate outcomes

#### Sanitary survey

In each of the five rounds of the household survey (October 2015; March, July and November 2016; and July 2017), the presence of feces both inside and outside the household compound, and within the *gott* will be observed. The practices of child feces disposal will also be assessed by administering a structured questionnaire and observation.

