To ensure objectivity and avoid information bias, latrine improvement status will be photographed with tablet PCs or mobile phones provided to enumerators and WaSH promoters. Assessments of the latrine improvement status will be made by supervisors and team leaders, not by the enumerators or WaSH promoters, which helps avoid overestimating the coverage of improved latrines. Latrine improvement status will be scored on the basis of the photos taken. Using the scored results, the degree of the effects of the improved latrines will be explored according to the improved status.

To avoid contamination between the intervention and control *gotts* in the same *kebelle*, we excluded any neighboring *gotts* of either intervention or control *gotts* from selection, thus making those *gotts* serve as a buffer zone [23]. In this trial, keeping records on the sanitation calendar is one of the most important features. In order to encourage mothers or caregivers to record diarrheal incidence every day, WaSH promoters will visit registered households on a weekly basis. The sanitation calendar will be photographed on this visit, and the supervisors and team leader will randomly revisit some of the households to verify the results. The system of encouragement and verification will be strictly maintained, particularly during the first 2 months of the intervention period, so the mothers or caregivers of registered households will be familiar with recording cases of diarrhea. A community meeting will be convened every month, and the WaSH promoter will correct substantial errors related to sanitation calendar utilization.

Our intervention is not to provide any financial nor material subsidy to community members. Rather, our intervention is to encourage community members to construct latrines for their own household members using locally available materials. We strictly comply with the key principles of Community-Led Total Sanitation (CLTS). Therefore, like all the previous studies, we have similar limitations such as the possibility of insufficient coverage.

This study will provide sound evidence for determining the effects of improved latrines on the prevalence, incidence density, and duration of diarrheal disease of children under five.

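### The diarrhoea calendar opens a month after CLTS begins, so incidence and duration have no calendar-based baseline and the recording window includes the mothers' learning weeks

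*Protocol article*

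**What the plan says.** All places are in the protocol article.

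- **Calendar.** Under Health outcome assessment with a sanitation calendar: "We distributed a sanitation calendar to all registered households beginning in December 2015". Mothers or caregivers mark it "every day over the 12-month period of longitudinal observation from December 2015 to November 2016". No run-in is described.
- **Intervention.** Under Study design, the CLTS procedures "will be carried out for latrine improvement beginning in November 2015 and will continue to October 2016". Triggering dates for individual gotts are not given.
- **Enrolment.** Under Household sampling methods, enumerators recruit the index child "from the fifth week of October through the second week of November 2015".
- **Learning to record.** The Discussion says encouragement and verification will be kept strict, "particularly during the first 2 months of the intervention period, so the mothers or caregivers of registered households will be familiar" with recording.
- **Endpoints.** Under Primary endpoint: "The primary endpoint of the study is diarrheal prevalence in children under 5 years of age". It is measured as 7-day prevalence in the household survey; incidence and duration are documented by the calendar.
- **Survey rounds.** Under Sanitary survey, the five rounds are dated "October 2015; March, July and November 2016; and July 2017", so round 1 is placed before CLTS.

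**The concern.** Incidence and duration rest on one instrument, and it is not in use until the intervention has begun. Gott rates vary widely on the protocol's own figures, so a baseline rate from the same instrument would be a useful covariate and would show whether the arms recorded alike before triggering. Without it, that precision and that check are unavailable.

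The protocol also expects mothers to need about two months to become used to recording, yet those weeks lie inside the stated observation period. If they are analysed, they bring in recording error at a time when latrines can have had little effect. The learning period is tied to the intervention period rather than to the calendar. Counted literally from November 2015, one of its two months has no calendar at all.

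**Working it through.** **1. Dates.** CLTS starts in November 2015 and the calendar in December 2015. Planned calendar weeks before CLTS begins: 0 in both arms.

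**2. The plan's own figure.** Inputs from Sample size calculation (incidence density): λ0 = 0.18, λ1 = 0.1422, 600 child-weeks per gott, k = 0.213422.

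c = 1 + (1.96 + 1.28)² × [(0.18 + 0.1422)/600 + 0.213422² × (0.18² + 0.1422²)] / (0.18 − 0.1422)² = 22.55

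This reproduces the stated 22.55. The 0.28 printed in the formula is a misprint for 1.28.

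**3. What baseline adjustment could gain.** The between-gott variance in the same section is 0.008199. With Poisson error, the reliability of a gott rate is 0.008199 / (0.008199 + 0.18/child-weeks).

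- Follow-up, 600 child-weeks: 0.008199/(0.008199 + 0.0003) = 0.965
- October round, 25 children × 1 week = 25 child-weeks: 0.008199/(0.008199 + 0.0072) = 0.532
- October round plus a four-week calendar run-in, 25 + 100 = 125 child-weeks: 0.008199/(0.008199 + 0.00144) = 0.851

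Share of gott-level variance removed = ρ² × baseline reliability × follow-up reliability, where ρ is the correlation of true gott rates over time. The documents do not give ρ; 0.5 to 0.8 is assumed.

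| Baseline used | ρ = 0.5 | ρ = 0.8 |
|---|---|---|
| October round | 0.128 | 0.329 |
| October round + 4 calendar weeks | 0.205 | 0.525 |

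The run-in therefore adds about 8 to 20 percentage points to what the October round can already supply.

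**4. Sensitivity to the variance input.** The sample size uses k = 0.213422, which implies a between-gott variance of 0.213422² × 0.18² = 0.00148, not 0.008199. Follow-up reliability is then 0.831, and baseline reliability is 0.170 (October) or 0.506 (October plus four weeks). The variance removed falls to about 4 to 9 % and about 11 to 27 %.

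**5. Cost of dropping two months.** With 24 gotts per arm and the printed k, power is Φ{(λ0 − λ1)/√V − 1.96}, where V = [(λ0 + λ1)/y + k²(λ0² + λ1²)]/23.

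- All 12 months, y = 25 × 52 = 1300 child-weeks: power 94.1 %
- Two months excluded, y = 25 × 43.3 ≈ 1083: power 93.7 %
- All 12 months kept, with no effect in the first two (assumption): the effect dilutes to 21 % × 10/12 = 17.5 %, power 82.4 %

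These power values hold only under the printed k. They compare the options and do not endorse the sample size.

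**The case against.** **A baseline exists.** Round 1 of the survey is dated before CLTS and gives 7-day prevalence in every gott. The sample size section also reports an earlier rate for the 48 gotts. The first point stands, so it would be wrong to say that there is no pre-intervention diarrhoea measurement or that gott variation cannot be adjusted for. The October round is a different instrument, though, and says nothing about duration. Recruitment also runs into the second week of November, so round 1 may touch the start of CLTS in some gotts. The earlier rate comes from the preliminary survey of March to May 2013, about two and a half years before the trial, and is a weak baseline.

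**No bias is shown.** A reader might infer that the late start biases the incidence comparison. The documents do not support that. Controls are randomised and concurrent, calendars go to all registered households on one schedule, and learning is shared by both arms unless support differs. Support could differ: the WaSH promoter section designates promoters in intervention gotts, while Sanitation mapping reads as if promoters cover all 48. That ambiguity is a separate question and does not establish differential recording.

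**The learning weeks may not be analysed.** A reader might also infer that they are counted as outcome. The article gives a 12-month recording period, a sample size based on 24 weeks, and no analysis window in Data analysis. The window may be set in an analysis plan that is not shown. What stands is that the recording period includes those weeks and that the 12 months and the 24 weeks are not reconciled. The stricter early verification is a real safeguard, and the sensible reading of the learning period is the first calendar months.

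**An earlier start may be impossible.** The article reports calendar distribution in the past tense, although Trial status says recruitment had not begun on 23 October 2015. If calendars are already out, only adjustment and exclusion remain.

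**Conclusion.** The point holds in a limited form. Incidence and duration have no calendar-based measurement before CLTS begins, and the recording window takes in the weeks when mothers are expected to be learning. The consequence is lost precision and early recording noise in secondary outcomes. The primary endpoint is unaffected.

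Most of what can be recovered cheaply comes from data already planned: about 13 to 33 % of gott-level variance through the October round, and about 21 to 53 % in total with four run-in weeks. These figures assume that true gott rates correlate 0.5 to 0.8 over time, that October prevalence tracks the same underlying gott rate as the calendar, that sampling error is Poisson (repeat episodes in one child would lower reliability), and that the between-gott variance is 0.008199. They are lower under the printed k, and lower again where kebelle stratification already explains part of the variation. Because triggering dates by gott are not given, some gotts may be triggered after the calendar opens, and the number of run-in weeks actually available is unknown.

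**What to change.** 1. Adjust the calendar outcomes for each gott's October 2015 7-day prevalence and for kebelle. This needs no new data.
2. If still possible, hand out and explain the calendar at the enrolment visit instead of in December. Use the weeks recorded before triggering, on the same dates in all gotts of a kebelle, as run-in and baseline, and exclude them from the outcome. The article describes kebelle strata, not matched pairs, so the dates should be aligned within the kebelle. The cost is earlier printing and earlier preparation of the promoters who check the calendars.
3. If the calendar cannot start earlier, name the first two calendar months as a training period excluded from the outcome in both arms. This supplies no baseline, but it removes the learning weeks. It costs 2 of 12 calendar months and leaves about 1083 child-weeks per gott against 600 planned, with a power loss of about 0.4 points under the printed k.

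Under any option, state which calendar weeks form the outcome, reconcile the 12-month recording period with the 24 weeks in the sample size, and define the two-month familiarisation period from the opening of the calendar.

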Much of the previous research investigating the effect of improved sanitation has been based on observational studies [8–11]. According to the results of a recent systematic review [12], few studies have involved a cluster-randomized controlled trial on sanitation intervention. Recently, several studies [13–15] have investigated the effect of improved sanitation, executing a cluster-randomized controlled trial. These studies did not demonstrate any protective effect of improved latrines against child diarrheal prevalence. However, none of the recent studies achieved universal or even a sufficient level of coverage required for fostering herd immunity. Without universal or at least a sufficient level of latrine coverage, the effect of improved latrines on the prevention of diarrheal disease is difficult to determine. Furthermore, most of the recent studies employing rigorous methodology have been conducted in South Asia. Since a number of people are living without improved sanitation in sub-Saharan Africa, a strong need exists for further evidence of the effect of improved sanitation in rural sub-Saharan Africa.

This study aims to explore the net effect of improved latrines on reducing diarrhea in children under five, particularly when latrine coverage reaches a certain threshold level. In addition, we aim to investigate the effect of improved latrines on the diarrheal duration of children by recording diarrheal incidence on a daily basis.

This study was designed as a cluster-randomized trial in the Southern Nations, Nationalities, and Peoples’ Region (the SNNPR State), Ethiopia, with the aim of finding evidence of the effect of improved latrines on diarrheal diseases in children under five. To our knowledge, this is the second study to assess the effects of improved latrines on child diarrheal reduction through the application of Community-Led Total Sanitation.

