#### Incidence density of diarrhea in terms of child-weeks

The expected value of the incidence density, E (*s*^2^), is given by$$ \mathrm{E}\left({\mathrm{s}}^2\right) = \lambda \mathrm{A}\mathrm{v}\left(1/{\mathrm{y}}_{\mathrm{j}}\right) + {\sigma^2}_{\mathrm{c}}=\lambda \mathrm{A}\mathrm{v}\left(1/{\mathrm{y}}_{\mathrm{j}}\right) + {\mathrm{k}}^2{\lambda}^2, $$

where λ is the true mean rate, *y*_*j*_ corresponds to the child-weeks of follow-up in the *j*^th^ cluster, Av() indicates the mean overall clusters, *σ*_*c*_^2^ is the between-cluster variance of the true rates, and *k* is the coefficient of variation of those rates [17]. Based on the preliminary survey, the overall diarrheal rate in the 48 *gotts* was 0.18 (or 18 cases per 100 child-weeks). The empirical standard deviation of the observed diarrhea rates was 0.092189, and the average of the reciprocal child-weeks per neighborhood was 0.001667. Therefore, *k* was estimated as$$ \begin{array}{c}\hfill {\sigma}^2={0.092189}^2-0.18\times 0.001667=0.008199,\hfill \\ {}\hfill \hfill \\ {}\hfill \mathrm{and}\;\mathrm{therefore},\;k=\surd \left(0.008199/0.18\right)=0.213422.\hfill \end{array} $$

We assumed that the diarrhea rate in the control *gotts* remained constant at λ_0_ = 0.18, and we required 90 % power (*z*_*β*_ = 1.28) if the intervention reduced the diarrhea rate by 21 %. Assuming 600 child-weeks of observation (24 weeks of follow-up for 25 children) in each *gott*, the number of neighborhoods required for each treatment group is given by c = 1 + (1.96 + 0.28)^2^[(0.18 + 0.1422)/600 + 0. 213422^2^(0. 18^2^ + 0. 1422^2^)]/(0.18 − 0.1422)^2^ = 22.55.

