### WaSH promoter

At the beginning of the implementation period, one (1) villager from each intervention *gott* will be designated and trained as a WaSH promoter to carry out post-triggering or follow-up CLTS activities in his/her *gott*. To ensure the coverage and quality construction of the latrines in each *gott*, and also the long-term utilization of the latrines to be built, these WaSH promoters will employ a combination of various approaches including technical advice on latrine construction, collective awareness-raising, and household visits.

For this purpose, during the initial phase of implementation, WaSH promoters in each *gott* will be trained on key issues regarding latrine construction and use. Once trained, these WaSH promoters are to be the leading agents to promote and follow-up on the latrine improvement and sanitation-related behavior change in the promoter’s respective Gott. More specifically, WaSH promoters will be responsible for activities including household visits, community conversations, technical advice on latrine design, organization of and participation in monthly review meetings with stakeholders, and so on. In line with the Ethiopian government’s CLTS Guideline, no material subsidies will be provided for the construction of individual household latrines. Instead, most of the resources, both human and financial, of the project are to be allocated for activities aimed at promotion of latrine construction and use, as well as the sanitation behavior change of the community.

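### Well-kept diarrhea calendars are rewarded with what will probably be soap and similar goods, a possible co-intervention in a trial of the net effect of latrines that a neutral gift would avoid

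*Protocol article*

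**What the plan says.** All passages are in the protocol article.

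- **Aim (Background):** "This study aims to explore the net effect of improved latrines on reducing diarrhea in children under five".
- **Who keeps calendars (Health outcome assessment with a sanitation calendar):** "We distributed a sanitation calendar to all registered households beginning in December 2015". Recording is daily "over the 12-month period of longitudinal observation from December 2015 to November 2016".
- **The reward (same section):** "A well-recorded calendar, regardless of whether it contains Os or Xs will be exchanged with a gift-in-kind", and the goods are "probably sanitation-related materials such as soaps, nail clippers, toothpastes, or the like". No date, frequency or quantity is given for the exchange.
- **Who supports recording (same section):** "WaSH promoters have been monitoring the recording status of the sanitation calendar on a weekly basis".
- **Where promoters are appointed (WaSH promoter):** one "villager from each intervention *gott* will be designated and trained as a WaSH promoter". No section describes the appointment of a promoter, or an equivalent, in control gotts.
- **Passages that suggest wider promoter activity:** Sanitation mapping covers every household in all 48 gotts and has the promoter do the marking. The Discussion has promoters visiting registered households each week, and registered households belong to both arms.

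**The concern.** The reward for recording the outcome may itself affect the outcome. The enrolled households keep the calendars behind incidence and duration, and they also answer the surveys behind the primary 7-day prevalence endpoint. The article does not treat hand hygiene as neutral: a hand-washing facility is one of the seven elements of its improved latrine.

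Two consequences are possible if the goods are received while diarrhea is being measured. With equal receipt, diarrhea could fall in both arms, leaving fewer events for latrines to prevent. The planning rates would then be too high: the 24 % prevalence, and for incidence the constant control rate of 0.18 ("We assumed that the diarrhea rate in the control"). With unequal receipt, part of the difference between arms would belong to the gift. Unequal receipt is possible because the gift depends on recording quality, and the people who coach recording are described as appointees of the intervention gotts.

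**Working it through.** **Inputs from the article.** Sample size calculation: prevalence 24 %, relative reduction 30 % (so 0.24 against 0.168), coefficient of variation k = 0.15, 80 % power, 48 gotts, 600 children per arm. Household sampling methods: 25 households per gott. CLTS implementation: 24 intervention gotts of 48. No significance level is stated for prevalence; I take 1.96 from the incidence formula.

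**Step 1. Reproduce the plan's figure.** For proportions with between-cluster variation,

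V = [p0(1 − p0) + p1(1 − p1)]/25 + k²(p0² + p1²)

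c = 1 + (1.96 + 0.8416)² × V / (p0 − p1)²

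V = (0.1824 + 0.1398)/25 + 0.0225 × (0.0576 + 0.0282) = 0.01289 + 0.00193 = 0.01482.

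c = 1 + 7.849 × 0.01482 / 0.005184 = 23.44, hence 24 gotts per arm, 48 in all and 600 children per arm. The stated figure is reproduced. (The design effect of 2.14 does not enter this formula.)

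Power with 24 gotts per arm is Φ(√[23 × (p0 − p1)²/V] − 1.96) = Φ(2.837 − 1.96) = 81 %.

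**Step 2. Equal receipt.** Assumptions, none of them in the documents: the goods cut diarrhea by 10 % or 20 % in recipient households, by the same factor in both arms; 90 % of households in each arm qualify; gifts arrive early enough to act during follow-up. Both prevalences are multiplied by 1 − 0.9 × 0.1 = 0.91 or by 1 − 0.9 × 0.2 = 0.82. The ratio stays at 0.70.

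| Assumed soap effect | Control | Intervention | Power |
|---|---|---|---|
| none | 0.240 | 0.168 | 81 % |
| 10 % | 0.218 | 0.153 | 77 % |
| 20 % | 0.197 | 0.138 | 72 % |

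**Step 3. Unequal receipt.** Assume that 90 % of intervention and 60 % of control households qualify. If latrines did nothing, the expected ratio would be

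- 10 % soap effect: (1 − 0.09)/(1 − 0.06) = 0.91/0.94 = 0.968
- 20 % soap effect: (1 − 0.18)/(1 − 0.12) = 0.82/0.88 = 0.932

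A true ratio of 0.70 would appear as 0.70 × 0.968 = 0.68 or 0.70 × 0.932 = 0.65.

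The direction depends on which arm qualifies more often. With the shares reversed (60 % intervention, 90 % control) the null ratio would be 0.94/0.91 = 1.03 or 0.88/0.82 = 1.07.

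**Step 4. Timing.** Calendars run from December 2015 to November 2016. The survey rounds are October 2015, March, July and November 2016, and July 2017. If calendars are redeemed as they are filled, the goods arrive during the first-phase comparison and Steps 2 and 3 apply. If they are redeemed once, after November 2016, the calendar outcomes and the first four rounds are untouched and only the July 2017 round could be affected. The text allows both.

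**The case against.** The strongest reply is that the harm needs facts the article does not state.

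- **Timing.** A reader might infer that the goods are handed out throughout the 12 months of recording. The article says only that a good calendar is exchanged. Redemption at the end would spare the first-phase results. This stands, and the point is conditional on it.
- **Staffing.** A reader might infer that promoters exist only in intervention gotts, so that the intervention arm will probably earn more soap. The WaSH promoter section describes them for intervention gotts but does not exclude others, and the calendar section, Sanitation mapping and the Discussion imply promoter activity for all registered households. Unequal receipt is possible, not shown. With equivalent support in control gotts, the directional bias would largely disappear.
- **Size.** The soap effect and the qualifying shares are assumed, and the gift itself is unsettled and includes nail clippers and toothpaste. The power figures also treat prevalence as one cross-section, although three post-baseline rounds fall in the first phase. All of this stands; the figures are illustrations.
- **Equal entitlement.** One rule applies to all registered households, whatever they mark. That guards against reporting shaped by the gift, and equal receipt leaves the ratio unbiased in the calculation above. It does not prevent a co-intervention, and equal entitlement is not equal receipt when the gift depends on recording quality.

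**Conclusion.** The concern holds in a limited form. The reward is a possible diarrhea-related co-intervention in the households that supply the outcomes, and neither its timing nor its delivery by arm is fixed. If it is redeemed during follow-up and received equally, it costs some power (81 % to 77–72 %) without biasing the ratio. If it is received unequally, it could account for part of any difference (a null ratio of 0.97–0.93 at 90 % against 60 %), which is modest beside the planned ratio of 0.70. Both ranges rest on an assumed 10–20 % soap effect and assumed qualifying shares.

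A reader might go further and conclude that the trial can no longer speak to a net effect of latrines. The documents do not support that. The package already contains hygiene promotion and hand-washing facilities (CLTS implementation), so it was never latrines alone, and the gift does not decide that question. What remains is an avoidable complication that is cheap to remove, and the word probably in the text shows that the choice of goods was still open.

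**What to change.** - Replace the hygiene goods with a gift of similar value that has no plausible link to diarrhea or its duration, for example a school exercise book or phone credit. Avoid salt and sugar: they can go into home-made rehydration drinks, and duration is an outcome.
- State one redemption schedule and one completeness rule, and apply both in all 48 gotts.
- Log the gifts given, by arm, so that equal receipt can be shown.

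**Cost.** The article gives no gift budget, but a gift of similar value should change it little. Logging is a small addition to the calendar checks already planned. The one downside is that the gift loses its sanitation theme.
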